### 2.3. Medication Dosing and Accountability

High-risk youth in the MED condition will be treated with escitalopram and monitored by a child and adolescent psychiatrist who is blinded to treatment assignment. Each high-risk participant will be assessed weekly for the first 4 weeks, then once every two weeks until 16 weeks. Escitalopram will be initiated at 5 mg daily for 1 week, then titrated to 10 mg daily for 1 week, then titrated to a target dose of 20 mg daily (maximum dose 30 mg/day). Titration will proceed no faster than 5 mg/week. Clinicians will carefully monitor participants for treatment response based on symptom severity rating scales of anxiety (PARS), depression (CDRS-R), (hypo)mania (Young Mania Rating Scale) [89], and the emergence of dysfunctional emotional arousal using the clinician-version of the Pediatric Adverse Events Rating Scale (PAERS) [90] and the parent-rated Treatment-Emergent Activation and Suicidality Assessment Profile (TEASAP) [91]. Escitalopram (or placebo) will be discontinued if there is a 2-step worsening on the Clinical Global Impression-Severity of Activation (CGI-SA) scale [91] compared with baseline and a Children’s Global Assessment Scale (CGAS) [92] score of <55.

Adherence, based on pill count, will be obtained at each visit. First, participants will receive weekly clinical follow-ups during dose titration, then clinical follow-ups every two weeks until week 16 to closely monitor for treatment adherence. Blood samples for analysis of serum escitalopram and desmethylescitalopram concentrations will be drawn at 8 weeks or at early termination if sooner than week 8. We aim to recruit medication-naïve youth but recognize that some high-risk youth who are seeking treatment for significant symptoms may be exposed to prior psychotropic medications. We will consider the role of past medications in our analysis of primary outcomes, and participants will be allowed to continue stable doses of concomitant stimulants and alpha-2 agonists. 

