#### 2.4.2. Pharmacogenetic Mediators

Our main pharmacogenetic-related mediators are *CYP2C19* metabolizer phenotype and serum escitalopram level. At 8 weeks or discontinuation of study participation (if earlier), we will obtain a sample for pharmacogenetic testing with the GeneSight Psychotropic assay. *CYP2C19* metabolizer phenotypes will be determined using Clinical Pharmacogenetics Implementation Consortium (CPIC) guidelines [99] and classified as normal (NM), rapid (RM), ultrarapid (UM), intermediate (IM), or poor (PM) metabolizer phenotypes. We will also perform a blood draw at 8 weeks or at early termination to determine serum escitalopram levels via mass spectrometry. Serum escitalopram concentration, *CYP2C19* metabolizer phenotypes, and medication adherence data will be integrated and modelled using MWPharm++ to determine pharmacokinetic parameters such as the maximum serum concentration (C_max_), the 24 h area under the curve (AUC_24_), the elimination half-life (t_1/2_), and clearance (CL) of escitalopram. Genetic testing reports will identify alleles in other genes as well (e.g., *CYP2D6*, *CYP2C9*, *CYP1A2*, *SLC6A4*, and *HTR2A*) and we will explore associations between these alleles and outcomes such as treatment efficacy and rates of adverse events. Based on similar studies of escitalopram in youth [64,65], we predict that high-risk youth with reduced *CYP2C19* metabolizer phenotypes will have higher C_max_ and/or AUC_24_ and higher rates of arousal symptoms than high-risk youth with normal or elevated *CYP2C19* metabolizer phenotypes.

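### The CYP2C19 phenotype–exposure prediction rests on dose-dependent C_max and AUC24 although dose at sampling can differ; a dose-normalised measured level is the better metric

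*Protocol article*

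**What the plan says.** All references are to the protocol article.

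- **Prediction (section 2.4.2).** Youth with reduced CYP2C19 "metabolizer phenotypes will have higher C_max_ and/or AUC_24_ and higher rates of arousal symptoms than high-risk youth with normal or elevated" phenotypes. The exposure part is worded on C_max and/or AUC24.
- **Dose (section 2.3).** Treatment starts at 5 mg for a week, moves to 10 mg for a week, and is "then titrated to a target dose of 20 mg daily (maximum dose 30 mg/day"). The speed limit is "Titration will proceed no faster than 5 mg/week".
- **Monitoring and stopping (section 2.3).** "Clinicians will carefully monitor participants for treatment response based on symptom severity rating scales", and emergent arousal is rated too. Study drug "will be discontinued if there is a 2-step worsening on the Clinical Global Impression-Severity of Activation (CGI-SA) scale" together with a CGAS score below 55. No other rule linking dose to response or arousal is printed.
- **Sampling (section 2.3).** Blood samples "will be drawn at 8 weeks or at early termination if sooner than week 8".
- **Pharmacokinetic model (section 2.4.2).** Serum concentration, CYP2C19 "metabolizer phenotypes, and medication adherence data will be integrated and modelled using MWPharm"++. The derived parameters include C_max and AUC24, and also "the elimination half-life (t_1/2_), and clearance (CL) of escitalopram".

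Section 2.6 names missed or extra doses as noise in the pharmacokinetic data. It does not mention differences in prescribed dose.

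**The concern.** The phenotype–exposure step asks whether reduced metabolizers clear the drug more slowly. C_max and AUC24 answer that directly only when dose is the same. Where dose differs between youth, these metrics combine metabolic capacity with the dose taken.

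Two consequences follow, and they differ in strength. The first needs no assumption about why doses differ: any spread of dose at sampling adds variance that has nothing to do with phenotype. The second is conditional: if the dose reached, or early termination, is related to arousal, and arousal is related to phenotype as the article predicts, then dose and phenotype pull exposure in opposite directions and the contrast is attenuated.

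Section 2.4.2 makes phenotype and serum level the main pharmacogenetic mediators, and section 2.5 makes escitalopram level a primary mediator. A real metabolic difference missed at this step would weaken the pharmacogenetic account of arousal that the study sets out to give.

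**Working it through.** **The plan's own figure.** The article gives no power or effect size for the CYP2C19 prediction. Its only power figure, 0.82 for amygdala change (section 2.5; d = 0.5, 100 against 50, two-sided alpha 0.05), reproduces: 0.5/√(1/50 + 1/100) = 2.887, and Φ(2.887 − 1.96) = 0.823 (0.818 with the t distribution). It has no bearing on this point.

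**Step 1: which doses can occur at sampling.** At 5 mg in week 1 and at most 5 mg more each week, 10, 15, 20, 25 and 30 mg are reachable at the earliest in weeks 2, 3, 4, 5 and 6. All precede week 8. A youth who stops in the first weeks is sampled at one of the lower steps. The permitted span is 30/5 = 6-fold.

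**Step 2: effect of dose on the contrast.** Under linear kinetics at steady state (assumed), AUC24 = F × dose / CL, so

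AUC ratio, reduced to comparator = R × (dose reduced / dose comparator), with R = 1/(1 − clearance reduction).

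The article gives no clearance difference, so a range is assumed.

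| Assumed clearance reduction | R (equal dose) | Full split, 20 vs 30 mg |
|---|---|---|
| 20% | 1.25 | 1.25 × 20/30 = 0.83 |
| 30% | 1.43 | 1.43 × 20/30 = 0.95 |
| 50% | 2.00 | 2.00 × 20/30 = 1.33 |

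Milder splits at the 30% reduction:
- half the comparators at 30 mg (mean 25 mg): 1.43 × 20/25 = 1.14
- one comparator in five at 30 mg (mean 22 mg): 1.43 × 20/22 = 1.30

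The predicted direction survives in both.

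**Step 3: variance and power.** Assumptions, none from the article: all 100 escitalopram youth sampled, 30 reduced and 70 normal or elevated, log-normal clearance with a CV of 40%, t-test on log AUC24. Power means significance in the predicted direction.

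*Same dose mix in both groups* (10, 15, 20, 25, 30 mg in 10, 10, 50, 10, 20%). The variance of log clearance is ln(1 + 0.4²) = 0.148. The variance of log dose in this mix is 0.094. Raw log AUC24 therefore has variance 0.148 + 0.094 = 0.243 (before rounding). The ratio stays at R, but simulated power at R = 1.25 is 0.54 raw against 0.74 dose-normalised; at R = 1.5 it is 0.96 against above 0.99.

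*Mildly different mix* (reduced 20, 20, 50, 5, 5%; comparators 5, 10, 50, 15, 20%; geometric mean dose ratio 0.81):

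| R | Raw AUC ratio | Power, raw | Power, dose-normalised |
|---|---|---|---|
| 1.25 | 1.01 | 0.03 | 0.76 |
| 1.5 | 1.21 | 0.43 | above 0.99 |
| 2 | 1.61 | 0.99 | above 0.99 |

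*Strongly different mix* (reduced 50% at 10, 25% at 15, 25% at 20 mg; comparators 5% at 15, 45% at 20, 20% at 25, 30% at 30 mg; dose ratio 0.57): raw ratios are 0.71, 0.85 and 1.13 for R = 1.25, 1.5 and 2. The first two are reversed. This is an extreme case.

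**Step 4: which dose-free metric.** Clearance is already derived, but phenotype is listed as an input to the model that produces it. A comparison of modelled clearance by phenotype would partly return what was put in. The measured serum concentration divided by the dose taken avoids this.

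**The case against.** The sentence in section 2.4.2 is a prediction, not a test specification, and a condensed article can leave dose handling to a fuller plan that is not shown. Clearance is among the derived parameters and cannot be obtained without dosing history, so nothing prevents a dose-free comparison. Achieved exposure is also a legitimate quantity for mediation, because arousal responds to the level reached. And the prediction is neither the primary clinical outcome nor the powered comparison.

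Much of this stands. The unseen plan may normalise for dose, and absolute exposure is right for the exposure–arousal link. What remains is that the article words the phenotype step on dose-dependent metrics when a better one is available from data already collected.

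A reader might go further and infer that reduced metabolizers will be on lower doses at week 8, so that the step is biased toward no effect or reversed. The article does not support that. It prints one common schedule with a shared 20 mg target; 30 mg is only a maximum; no rule for going above target or lowering dose is given; and the only printed action tied to activation is discontinuation. If nearly all youth are at 20 mg when sampled, the mixing is small.

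**Conclusion.** The point holds in a limited form. C_max and AUC24 are a poor basis for the phenotype–exposure prediction in a design that permits different doses at sampling and samples early leavers when they stop.

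The loss of precision depends only on dose varying at sampling; in the illustration it lowers power from 0.74 to 0.54 at R = 1.25 and matters little at R = 1.5 or above. Attenuation additionally requires dose or early termination to be related to arousal, and so to phenotype, which is plausible from the monitoring and stopping text but not stated. Reversal requires an extreme split together with an assumed clearance difference. The clearance ratios, phenotype split, CV and dose mixes are all assumptions, and the arithmetic assumes linear kinetics at steady state. The primary outcome and the stated power are untouched.

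**What to change.** - Test the phenotype–exposure prediction on measured serum escitalopram concentration per mg of dose taken before sampling.
- Use clearance as supportive evidence only, and only if it is estimated without phenotype as a model input.
- Keep absolute C_max and AUC24 for the exposure–arousal (mediation) question.
- Report dose at sampling by phenotype, and show which samples came from early termination, since these may not be at steady state.

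The cost is analysis wording. Serum levels and pill counts at each visit are already planned, and the prescribed dose is known from the trial's own records. No dosing rule, visit or sample changes.

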### 2.5. Hypotheses and Analytic Plan

Our core analytic strategy is mixed-effects modeling [100] utilizing baseline and highest levels of arousal assessed between 4–16 weeks as our primary outcome. In the mixed effects analysis, change in arousal (baseline to post, where post is defined as the highest level of arousal recorded between 4 and 16 weeks) will be the outcome predicted by treatment status (MED vs. No MED); escitalopram levels and neural changes will be the primary mediators. This method was chosen for improved precision (power) and better handling of missing data compared to approaches that use single change scores or analysis of covariance. We will use the MacArthur framework [101,102], which will be embedded in our mixed-effects modeling, to investigate treatment effect mediators, moderators, and nonspecific predictors. We have chosen this framework as the preferred approach to define and test mediation because this framework allows for stronger inferences regarding temporal relations, and the research question posed has significant implications for clinical decision-making [102].

Power estimation for mediation hypotheses was conducted using Monte Carlo simulations based on a single longitudinal mixed-effects model. Previous studies showed effect sizes ranging from d = 0.6 to 1.8 for the effect of antidepressant medication on neural outcomes [20,49]. We assumed a conservative effect size of d = 0.5 given that we will measure changes in neural outcomes early on (4 weeks). We allowed a moderate difference across the two sites (d = 0.6 vs. d = 0.4, on average d = 0.5). Under this scenario, with the initial N = 150 (Stanford:50 MED, 25 No MED; UC:50 MED, 25 No MED), the estimated power to detect the treatment effect (MED vs. No MED) on change in amygdala hyperactivity is 0.82 (two-tailed, alpha = 0.05).

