### 2.2. Randomization

High-risk youth will be randomized to receive double-blinded treatment with psychotherapy plus escitalopram (MED) vs. psychotherapy plus placebo (No MED) in a 2:1 ratio using block randomization with a block size of six. Randomization will be stratified within sites with respect to diagnoses (anxiety only, depression only, or anxiety and depressive symptoms), family history load (i.e., ≥3 first- or second- degree relatives with bipolar disorder vs. 1–2 first- or second-degree relatives with bipolar disorder), and the presence (vs. absence) of concomitant stimulant or alpha-2 agonist treatment. 

We selected psychotherapy (No MED) as the most ethically reasonable comparator for youth presenting with clinically significant symptoms of depression or anxiety. All participants (No MED and MED) will be assigned a study-trained therapist who will provide hour-long, up to weekly, individual cognitive-behavioral therapy or family-focused therapy (FFT) for high-risk youth [87,88]. FFT is a semistructured treatment that is protocol-driven and incorporates psychoeducation about mood and stress vulnerability models for depression/anxiety, structured communication training among family members, and problem-solving skills. Sessions will be weekly for the first 4 weeks, then participants will be given the option to continue meeting weekly or once every two weeks for an additional 12 weeks.

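### With one baseline and one post value per participant, the mixed model has no precision advantage over analysis of covariance, and is less precise if baseline means are left free by arm

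*Protocol article*

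**What the plan says.** Section 2.5 of the protocol article describes the core strategy as "mixed-effects modeling [100] utilizing baseline and highest levels of arousal assessed between 4–16 weeks as our primary outcome". It adds that "post is defined as the highest level of arousal recorded between 4 and 16 weeks", so each participant contributes two values. The change between them "will be the outcome predicted by treatment status (MED vs. No MED"). The method was "chosen for improved precision (power) and better handling of missing data compared to approaches that use single change scores or analysis of covariance".

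The neural outcome has the same two-point structure, with scans at baseline and at 4 weeks (section 2.4.1).

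The only power figure concerns that neural outcome. The inputs are "We assumed a conservative effect size of d = 0.5 given that we will measure changes in neural outcomes early on (4 weeks") and "with the initial N = 150 (Stanford:50 MED, 25 No MED; UC:50 MED, 25 No MED"), and the power for the treatment effect on "change in amygdala hyperactivity is 0.82 (two-tailed, alpha = 0.05").

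The article does not say whether the two arms share a baseline mean in the model or whether baseline enters as a covariate. It gives no covariate list.

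**The concern.** A mixed model can gain on ANCOVA when it has several follow-up values per participant to draw on. Here the PAERS ratings from week 4 onward (every two weeks to week 16, section 2.4) are reduced to one maximum before modelling, and the neural analysis has a single planned follow-up scan. With two values per participant, the familiar comparison between change scores and ANCOVA applies, and the article states its result the wrong way round or, at best, claims an advantage that is not there.

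This is an affirmative statement about the core analysis, not a detail that an article leaves to a later document. If the team relies on it and fits free baseline means, it gives up precision on the primary clinical outcome and on neural change, although the baseline values needed to avoid that are already collected. The issue is efficiency. No bias or type I error problem follows from it.

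**Working it through.** **Inputs.** From section 2.5: 100 MED and 50 No MED, d = 0.5, two-sided alpha 0.05, stated power 0.82, one baseline and one post value. Assumed, because the article gives neither: the baseline-to-post correlation ρ (0.3, 0.5, 0.7) and, unless noted, equal standard deviations (SDs) at both times.

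**1. The stated power.** √(1/100 + 1/50) = √0.03 = 0.1732, and 0.5/0.1732 = 2.887. Power = Φ(2.887 − 1.96) = 0.823. The noncentral t with 148 degrees of freedom gives 0.818. Both agree with 0.82. A plain two-sample comparison with d in units of the SD of change is enough to produce the figure.

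**2. Free baseline means, complete data.** In one simulated data set (100:50, ρ = 0.5), the time-by-treatment effect in the mixed model was 0.48869 (SE 0.14793). The two-sample comparison of change scores gave the same estimate and SE. ANCOVA on the same data had SE 0.1420.

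**3. Large-sample variances.** Let σ0 and σ1 be the baseline and post SDs.

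- Change score: σ0² + σ1² − 2ρσ0σ1
- ANCOVA: σ1²(1 − ρ²)
- Difference: σ0² − 2ρσ0σ1 + ρ²σ1² = (σ0 − ρσ1)², which cannot be negative

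With equal SDs the ratio of ANCOVA to change is (1 − ρ²)/[2(1 − ρ)] = (1+ρ)/2. Power is for 100:50 and d = 0.5, on two readings of d:

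| ρ | Change 2(1−ρ) | ANCOVA 1−ρ² | Ratio | d in change SDs: change → ANCOVA | d in single-time SDs: change → ANCOVA |
|---|---|---|---|---|---|
| 0.3 | 1.40 | 0.91 | 0.65 | 0.823 → 0.947 | 0.684 → 0.857 |
| 0.5 | 1.00 | 0.75 | 0.75 | 0.823 → 0.915 | 0.823 → 0.915 |
| 0.7 | 0.60 | 0.51 | 0.85 | 0.823 → 0.879 | 0.961 → 0.981 |

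With a post SD of 1.5 or 2 times the baseline SD, change variance over ANCOVA variance ran from 1.00 to 1.84 for ρ from 0.1 to 0.9. The loss can vanish (when σ0 = ρσ1), but it never turns into a gain.

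**4. Common baseline mean, and missing post values.** Empirical SEs of the arm effect from 1,500 simulations per row, with the mixed models fitted at known covariance and post values missing completely at random:

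| ρ | Post missing | Change score | Mixed, free baseline | ANCOVA | Mixed, common baseline |
|---|---|---|---|---|---|
| 0.3 | 0% | 0.2098 | 0.2098 | 0.1684 | 0.1676 |
| 0.3 | 20% | 0.2322 | 0.2249 | 0.1919 | 0.1902 |
| 0.5 | 0% | 0.1762 | 0.1762 | 0.1516 | 0.1507 |
| 0.5 | 20% | 0.1890 | 0.1846 | 0.1667 | 0.1663 |
| 0.7 | 0% | 0.1388 | 0.1388 | 0.1265 | 0.1257 |
| 0.7 | 20% | 0.1519 | 0.1500 | 0.1420 | 0.1412 |

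The common-baseline model is within about 1% of ANCOVA throughout. In the single data set of step 2, a common-baseline random-intercept fit reported SE 0.1324 against ANCOVA's 0.1420. That is a model-based SE from a fit that forces one variance at both times, and the repeated simulations show no such gain.

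**The case against.** The strongest reply is that the article never says baseline means are free by arm. Treating both baseline and the highest level as outcomes in a longitudinal model is compatible with a common baseline mean, and that model loses nothing to ANCOVA. This stands, and it makes the loss of power conditional. It does not rescue the sentence, because matching ANCOVA is not improving on it.

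A second reply is that the rationale also cites missing data. That stands in part. With post values missing, even the free-baseline model gained slightly on complete-case change scores. The check covered missing post values only, so it does not dispute the missing-data rationale in general. It shows only that the precision claim against ANCOVA is not recovered this way.

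Third, the size rests on an assumed ρ and equal SDs. Equal SDs are doubtful for PAERS, whose post value is a maximum over several visits. This also stands: the ordering is general, the amount is not.

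Two stronger readings are tempting and are not supported:

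- A reader might infer that the stratification factors are left out of the model, since section 2.2 says "Randomization will be stratified within sites with respect to diagnoses (anxiety only, depression only, or anxiety and depressive symptoms", with further factors, while section 2.5 names only treatment as predictor. The article gives no covariate list, and an article commonly leaves that to the full protocol or analysis plan. Section 2.5 also allows the effect to differ by site in the power simulation and mentions moderators and nonspecific predictors. Silence here is not an omission.
- A reader might infer that the 0.82 is wrong or that the trial is underpowered. The figure reproduces from its own inputs. It concerns amygdala change, and the article gives no power for PAERS.

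**Conclusion.** The claim of better precision than ANCOVA is unsupported under either way of handling baseline. With free baseline means and complete data, the model is the change-score analysis, and its large-sample variance exceeds ANCOVA's by (σ0 − ρσ1)², which is zero or more. With a common baseline mean it is about equal to ANCOVA.

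Under the free-baseline reading, equal SDs and an assumed ρ of 0.3, 0.5 or 0.7, ANCOVA would reach the same precision with 65%, 75% or 85% of the participants. Under the common-baseline reading nothing is lost and only the wording is wrong. Making change the outcome favours the first reading without settling it. The point deserves correction because it misstates a property of the core analysis and the remedy is nearly free.

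**What to change.** State how baseline is handled, in one of two ways:

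- In the mixed model, give MED and No MED one common baseline mean, which randomisation justifies because baseline precedes it. Let the variances at the two times differ, since the post value is a maximum.
- Analyse the post value with baseline as a covariate: baseline PAERS for arousal, baseline activation for neural change.

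Then delete the claim of better precision than ANCOVA, or replace it with a statement that the model is expected to be about as precise. The missing-data reason can stay if worded separately. If the full protocol or analysis plan already specifies one of these options, only the sentence needs correcting.

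The cost is analysis wording. No new data or visits are needed and the sample size is unchanged, because the baseline values are already collected before randomisation.

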## 2. Study Protocol

### 2.1. Setting and Study Population

We will recruit 150, 12- to 17-year-old youth with significant depressive or anxiety symptoms, based on responses to Children’s Depression Rating Scale-Revised (CDRS-R) [81] and the Pediatric Anxiety Rating Scale (PARS) [82] clinical interviews and 60, 12- to 17-year-old healthy control youth (ClinicalTrials.gov Identifier: NCT02553161, first posted 17 September 2015). Youth with significant depressive or anxiety symptoms will be included in our study, and psychotherapy and the study medication (escitalopram) will be provided to study participants to treat their depressive and/or anxiety disorders. Although participants’ DSM-5 diagnoses will be assessed using KSADS, we will not require a specific diagnosis for inclusion and will only exclude participants with the following diagnoses: bipolar I or II disorder, autism spectrum disorders, obsessive compulsive disorder, post-traumatic stress disorder, Tourette’s disorder, or any psychotic disorder including schizophrenia. Our inclusion and exclusion criteria are summarized in Table 1. Healthy controls will receive behavioral, neural, and physiological assessments at baseline only. First-degree relatives will be assessed using the Structured Clinical Interview for Diagnostic and Statistical Manual (SCID) [83] and the Family History-Research Diagnostic Criteria (FH-RDC). We will also compare our findings to those of a recently published double-blind, placebo-controlled trial using the same neuroimaging task and the same medication, but in youth *without* a family history of BD [84].

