#### 2.4.1. Neural Mediators

Our main neural outcomes are defined by prior studies implicating amygdala and VLPFC activation. We will evaluate activation in these regions during the emotional-neutral contrast of the Continuous Performance Task with Emotional and Neutral Distracters (CPT-END) task, a task of sustained attention with emotional and neutral pictures which we have used in our prior work examining prefrontal-limbic connectivity [94,95]. To assess the complex prefrontal-limbic circuit mechanisms that subserve antidepressant-related arousal both intrinsically at rest and during emotional arousal, youth will complete a resting state scan followed by the CPT-END in the MR scanner. Connectivity during the CPT-END and at rest will also be assessed. MRI data will be acquired at baseline for high-risk youth and controls, and at 4 weeks in high-risk youth using a 3.0 Tesla GE whole-body MRI scanner located at Cincinnati Children’s Hospital Medical Center Imaging Research Center and Stanford’s Richard M. Lucas Center for Imaging. An additional MRI scan will be acquired in any high-risk youth who develops antidepressant-related dysfunctional emotional arousal prior to 4 weeks, or up to one additional scan after 4 weeks if a hyperarousal event occurs between 4–16 weeks.

Participants will complete two fMRI runs of the emotionally arousing CPT-END task, in which whole-brain images (volumes) will be acquired every 3 s using a T2*-weighted gradient-echo echo-planar imaging pulse sequence. We will explore whether high-risk youth who do not develop antidepressant-related arousal benefit from antidepressant treatment, which has been documented to reduce amygdalar activation [96]. For those high-risk youth who are not exposed to escitalopram, we predict that there will be effects on limbic activation and connectivity due to a combination of psychotherapeutic effects [97], trait vulnerability to prefrontal-limbic dysfunction [35], and a natural propensity toward symptom progression [98]. We hypothesize that early change (baseline to 4 weeks) in the level of amygdala hyperactivity will predict the level of subsequent arousal (highest after the 4-week scan) and that the correlation between changes in neural circuitry and the level of subsequent arousal is stronger in the MED condition compared to the No MED condition (Figure 2).

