### 2.6. Limitations

The proposed study will gather data on high-risk youth only during a 16-week period, so this study cannot determine whether there are long-term risks or delayed effects of antidepressant exposure in high-risk youth far beyond the duration of the study. We expect that most children who enroll in our study may still live with their first-degree relatives with BD, so our study cannot easily differentiate between the mental health risks posed by heritable genetic factors as opposed to the stress of living with a family member (especially a parent) with a serious psychiatric disorder. Treatment adherence will be well-tracked, but achieving reliable medication adherence in adolescents remains challenging. Even though minor lapses in medication adherence may have relatively little effect on clinical or neuroimaging outcomes, missed or extra doses may introduce significant noise into pharmacokinetic data. For example, serum escitalopram levels can vary greatly when doses are missed in the week before blood samples are drawn. Furthermore, youth who experience hyperarousal symptoms may be more distressed and consequently less likely to participate in some inherently stressful aspects of the study, such as entering the MR scanner or providing a cheek swab or blood sample for pharmacogenetic analysis. Finally, we expect that most youth enrolled in this study will be medication-naïve, but some study participants may be allowed to take concomitant psychostimulants or alpha-2 agonists before and during the study, and this may also confound results.

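### The 0.82 offered as power for the mediation hypotheses covers only the treatment-to-amygdala link, so it is an upper bound for mediation and does not support those hypotheses

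*Protocol article*

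**What the plan says.** The power paragraph in section 2.5 of the protocol article opens: "Power estimation for mediation hypotheses was conducted using Monte Carlo simulations based on a single longitudinal mixed-effects model". It then gives one effect size, for medication on neural change: "We assumed a conservative effect size of d = 0.5 given that we will measure changes in neural outcomes early on (4 weeks". Site variation is built in: "We allowed a moderate difference across the two sites (d = 0.6 vs. d = 0.4, on average d = 0.5". The figure is computed "with the initial N = 150 (Stanford:50 MED, 25 No MED; UC:50 MED, 25 No MED") and the result is that "the estimated power to detect the treatment effect (MED vs. No MED) on change in amygdala hyperactivity is 0.82 (two-tailed, alpha = 0.05").

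Section 2.4.1 sets out what is to be shown about mediation. Early amygdala change should predict the later peak in arousal, and the "correlation between changes in neural circuitry and the level of subsequent arousal is stronger in the MED condition compared to the No MED condition". Section 2.5 adds that the MacArthur framework will be embedded in the mixed-effects model, and it names escitalopram level as a further primary mediator. None of these parts has an effect size or a power.

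The recruitment target in section 2.1 is the same number as in the power calculation: "We will recruit 150, 12- to 17-year-old youth with significant depressive or anxiety symptoms". Section 2.6 warns that youth with hyperarousal may be "less likely to participate in some inherently stressful aspects of the study, such as entering the MR scanner".

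**The concern.** The label and the figure do not match. The paragraph promises power for mediation and delivers power for the effect of treatment on the mediator. Mediation by prefrontal-limbic change is aim (b) in the abstract, and this is the only power figure in the article. If mediation is not found, readers may set the null result against 82% and call it a reasonably powered negative, although that figure was not calculated for the test in question.

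The number of scan pairs behind the figure is a second, weaker concern. The calculation uses every youth to be recruited, while the limitations section foresees that some may be unwilling to be scanned, and that this may be related to the outcome.

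**Working it through.** **Inputs from the article.** d = 0.5; 100 MED and 50 No MED; two-sided alpha 0.05 (section 2.5). **Inputs assumed here, because the article gives none.** Scan-loss rates, the partial correlation of amygdala change with later arousal given treatment, and the correlations within each arm.

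**1. Reproducing 0.82.** The non-centrality is d / √(1/n₁ + 1/n₂) = 0.5 / √(1/100 + 1/50) = 0.5 / 0.1732 = 2.887. The normal approximation gives Φ(2.887 − 1.960) = 0.823, and the non-central t gives 0.818. A simulation with a site term and site effects of 0.6 and 0.4 also gives about 0.82. A one-sided test (0.893) and a 75:75 split (0.865) do not match. The figure is thus the two-group power for the first link with 150 complete pairs.

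**2. First link with fewer usable pairs** (same non-central t, loss equal in both arms):

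| Assumed loss | Pairs | Power |
|---|---|---|
| 0% | 100 vs 50 | 0.818 |
| 10% | 90 vs 45 | 0.776 |
| 20% | 80 vs 40 | 0.726 |

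The normal approximation gives 0.823, 0.782 and 0.733 for the same rows.

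**3. The ceiling.** A mediation claim requires the first link together with a mediator-outcome effect or a treatment-by-mediator interaction. The probability that both conditions are met cannot exceed the probability of the first. At d = 0.5, joint power therefore cannot exceed about 0.82, whatever the second link is.

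**4. Joint power.** The second-link power is Φ(atanh(r)·√(n − 4) − 1.960), and joint power is its product with first-link power. With n = 150, √146 = 12.083.

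- r = 0.2: 0.2027 × 12.083 = 2.449; power 0.688; joint 0.688 × 0.818 = 0.56.
- r = 0.3: 0.3095 × 12.083 = 3.740; power 0.962; joint 0.962 × 0.818 = 0.79.
- r = 0.4: 0.4236 × 12.083 = 5.119; power above 0.999; joint 0.82.

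With 120 pairs the joint figures are 0.43 at r = 0.2 and 0.66 at r = 0.3. A joint-significance simulation (4,000 runs per setting) agrees: 0.57, 0.78 and 0.81 with 150 pairs for r = 0.2, 0.3 and 0.4, and 0.40 and 0.66 with 120 pairs for r = 0.2 and 0.3.

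**5. A stronger correlation under MED.** For two independent correlations, SE = √(1/97 + 1/47) = 0.178, and power is Φ(Δz/SE − 1.960).

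- 0.5 vs 0.3: Δz = 0.549 − 0.310 = 0.240; power 0.27.
- 0.4 vs 0.1: Δz = 0.424 − 0.100 = 0.323; power 0.44.
- 0.5 vs 0.1: Δz = 0.449; power 0.71.

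Power of 80% needs Δz = (1.960 + 0.842) × 0.178 = 0.50, for example 0.5 vs 0.05. This comparison taken alone is not bounded by 0.82. It is a different test and needs its own calculation.

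**The case against.** The strongest reply is that the article states no mediation power at all. The sentence with 0.82 names the effect it refers to, and a careful reader will not mistake it. This stands in part: the number is correctly described where it appears. It does not remove the mismatch, because the paragraph presents that number as the outcome of power estimation for mediation.

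A reader might infer that the trial lacks 82% power for mediation. The document does not establish this. It gives no second-link effect, and with a partial correlation of 0.4 or more and complete scans, joint power is about 0.82 as well. If the true first-link effect were d = 0.6, first-link power would be 0.93 (normal approximation).

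A reader might also infer from the exact match that the calculation has no allowance for lost scans. This is likely but not proven. The simulation settings are not shown, the N is called initial, and the article does not say whether d is scaled to the SD of change or of the raw measure. If d is on the raw SD and the pre-post correlation is 0.6 (assumed), the SD of change is √(2 × 0.4) = 0.894 and d for change is 0.5 / 0.894 = 0.559. With 80 vs 40 pairs the non-centrality is 0.559 / 0.1936 = 2.887, and power is again about 0.82. Subtracting 20% from the stated figure could then count the loss twice. Section 2.6 gives no loss rate, and section 2.4.1 provides an extra scan for youth who develop arousal before week 4. The mixed model does keep youth with only a baseline scan, but they add little information on change.

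Finally, an article may leave power details to the full protocol or SAP. That would excuse silence on mediation power. It does not excuse announcing mediation power and giving the power of a different test. The article also does not say that N = 150 was derived from this figure, so that should not be claimed.

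**Conclusion.** The point holds as a mislabelled power claim. It is not an arithmetic error: 0.82 reproduces. Under the article's own d = 0.5 it is an upper bound for any joint mediation test, and it does not support the hypotheses it is offered for. This ceiling needs no outside assumption.

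The size of the gap does need assumptions. With complete data it runs from none, at a partial correlation of 0.4 or more, to a joint power of 0.56 at 0.2. The between-arm difference in correlation is poorly powered for moderate differences even with all 150 pairs. The scan-loss component applies only if 0.82 assumes complete pairs, which the match suggests but cannot confirm. Severity is moderate: no analysis or sample size is wrong, but the reading of a null mediation result is affected.

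**What to change.** In section 2.5:

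- Describe 0.82 as power for the treatment effect on amygdala change only, and state the number of usable scan pairs it assumes and the SD to which d is scaled.
- If it assumes complete pairs, restate it over a range of loss, for example 0.78 at 10% and 0.73 at 20% (assumed rates).
- From the same simulation, report power for the joint mediation test and for the treatment-by-mediator interaction over stated second-link effects.
- Describe as exploratory any of these analyses that is not adequately powered.

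The cost is a rerun of an existing simulation and a reworded paragraph. N does not change. The downside for the sponsor is a less favourable stated figure.
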